**Summary of changes**

**AMENDMENT #1**

1. We propose to change the milk substitute from the almond/coconut milk substitute to a milk substitute manufactured by Mead-Johnson. This substitute will be made of constituent amino acids and will be a match +10% the USDA estimates for nutrients in fortified whole cow’s milk. As the milk substitute will be flavored, Mead Johnson will also provide individual packets of flavoring that can be added to the cow’s milk arms to ensure comparability. They are also exploring producing a vitamin-D fortified flavoring that can be added to unfortified cow’s milk most widely available in Mongolia. We will provide an amendment letter with specifics as they become available.

There are several advantages of the Mead Johnson milk substitute over the almond/coconut milk we originally proposed: 1) it will be better scientifically than the almond/coconut milk because the amino acids are a closer match to cow’s milk; 2) the formula is hypoallergenic, so it is less likely to cause allergic reactions than the almond/coconut milk, and we could include children with nut or wheat allergies (who had to be excluded using the almond/coconut milk); 3) the formula will either be delivered as a powder to be mixed at the Guum plant or will be delivered in pre-mixed cans, instead of being mixed by hand by milk monitors at the school. This will improve hygiene, as well as ensure more precision in the actual intervention delivered.

Mead Johnson has indicated that they will provide these products to the study at no cost.

2. We will obtain the vitamin supplements from Tishcon Corporation. The Tishcon Corporation is a well-established company that produces vitamin and mineral supplements. Several of our colleagues have used Tishcon for their research projects involving supplements, because of the high quality control and the ability of Tishcon to produce supplements with precise vitamin quantities. In particular, Tishcon is willing to manufacture the vitamin supplements taking into account the normal degradation that happens over time to any supplement (such as might happen between the beginning and end of the 3 month trial), so that we will actually deliver the precise amount that we have proposed. Tishcon has offered to donate the supplements for this project, considering the project goals.

3. In deference to issues raised by the Mongolian ERB, we have eliminated the Tanner examination by the trained medical students. Instead, we will ask the children to complete a pencil-and-paper questionnaire (attached) which has been used by children in other studies (notably, the Growing Up Today Study) to indicate their level of pubertal development. We feel it is necessary to include some assessment of pubertal development, due to the study’s intention to measure growth. It is important to understand where in their growth spurt that children might be, and the best way we know to assess this is to have some measure of pubertal development. The ERB also suggested that the Child Evaluation Form has too many open-ended questions. We have added response choices to most of the questions.

4. We propose to supplement the Cognitive Performance Test with a 5-minute processing speed subtest of the Wechsler Intelligence Scale for Children (WISC). The test will be administered at the beginning and end of the study to see whether the nutrients provided in the milk improve children’s cognitive performance over three months.

5. We have replaced the more intensive dermatologic examination with a more simple self-report and examination of flexural dermatitis (dermatitis at skin creases, such as elbows and knees), better suited to trained medical student administration

6. Urine assay: We propose to test first morning urine void urines using the “whizpop” (pee-on-a sponge) collection kit, which we have used successfully with 6-8 year olds in Boston. The children will be given the collection kit to take home. They will test for three sequential days at the start of the study and three at the conclusion. We have added first morning urine samples because we have colleagues who report being close to developing urine-based growth hormone assays. Since growth hormone is highly variable, use of three measures at baseline and three at trial completion would provide a more stable estimate of change in growth hormone due to the intervention. Measurement of growth hormone is a primary aim of this study, so we are hopeful that the assay development will be successful. At present, we do not have a budget to cover these assays, but will seek funds if the assay development is successful.

1. Change to the consent/assent forms: We added a sentence on each form that states that “although the child's parents agree to participate in the study the child's decision will be respected”. We have made changes to reflect the use of the Mead Johnson milk substitute instead of the almond/coconut milk.

**AMENDMENT #2**

1. Mead-Johnson has completed their development of a milk substitute, and we include here its final nutritional content. There is a slight (13-23 calories per 8 ounces) difference in the calories of the milk substitute compared to the Mongolian and American milk, attributable to the slightly higher carbohydrate content of the milk substitute compared with cow’s milk. Furthermore, the US cow’s milk is somewhat more calorie dense than Mongolian cow’s milk. To maintain nutritional consistency and balance carbohydrate intake across the milk study arms, we propose to give the children low-fat crackers as part of the study protocol. We will give children enough low-fat crackers so that each arm will be comparable in terms of carbohydrates and calories.
2. The Mongolian milk producer, Guum, will also mix and package the milk substitute on a daily basis.
3. There will be no additional flavoring added to the American or Mongolian milks.
4. **In order to enroll children ages 9-11, we have elected to include 4^th^ grade classrooms in addition to the 3^rd^ grade.**

As promised, we are submitting the final version of the Food Frequency Questionnaire, now refined with the input of colleagues from the Mongolian Public Health Institute.

**AMENDMENT #3**

**In our original application, we proposed to enroll students from 10 different schools to ensure that this would allow us to enroll a total of 750 children in the study. During our September visit, we discovered that some of our targeted schools have gown rapidly as a result of increases in area populations due to immigration from the countryside. This influx of students allows us to recruit children from two schools, rather than 10. We decided to adopt this change due to budget constraints and logistic considerations.**

We have recently learned that the school vacation schedule we were originally given by the Ministry of Education is not correct for the two schools (#62 and #65) from which we will recruit students. Instead of a one week February break, the children will have vacation from January 17-25 and March 22- April 5. We had originally planned to run the intervention from January 19 through the end of March, on schooldays only. **We have regrouped with our Mongolian colleagues and the schools to change the schedule to fit the intervention in between the two vacations: from January 26-March 20, including weekends.** (During our pilot study in School #65 in 2005, the intervention was daily, including weekends).

The children in the milk arms will receive milk daily (a total of 300 IU), and children in the daily vitamin D dose arms will receive 300 IU supplements daily (instead of 5 days per week). **The intervention will still run the same total number of days.**

The children in the ‘monthly dose’ group were originally intended to receive between 1000-2000 IU over 3 days at the beginning of each month, for a total of 15000 IU over three months, the equivalent vitamin D dose as the milk and daily supplement groups. The intention was to compare the effectiveness of a once monthly supplement (easier to administer from a public health standpoint) to a once daily supplement. So that we can measure plasma vitamin D levels in the ‘monthly’ group at their nadir, we planned to draw the plasma at about 30 days after the last monthly dose.

Now that we are compressing the daily milk and daily supplement intervention into approximately 50 days instead of three months by including weekends, we also need to deliver the ‘monthly’ dose in approximately 50 days. We propose to do this by giving the children 1700-2000 IU per day for 7 days at the beginning of the trial.

In fact, the Mongolian public health system typically gives 50,000 IU once a year at the beginning of winter to infants at risk of rickets, so this strategy is familiar to them.

A daily vitamin D dose of 200-2000 IU is within the tolerable upper limit of 2000 IU per day published by the Institute of Medicine, ^1^ and well below the level at which toxicity has ever been observed (40,000 IU per day).^2^ We therefore are confident that this schedule change does not increase the risks of this study above minimal risk.

^1^Standing Committee on the Scientific Evaluation of Dietary Reference Intakes FaNB, Institute of Medicine: Dietary Reference Intakes for Calcium, Phosphorus, Magnesium, Vitamin D, and Fluoride. National Academy Press, Washington, D.C., 1997. Available online at <http://books.nap.edu/openbook.php?record_id=5776&page=285>

^2^ Vieth R, Chan P-CR, MacFarlane GD. Efficacy and safety of vitamin D3 intake exceeding the lowest observed adverse effect level. Am J Clin Nutr 2001;73:288-94.

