4. 300 IU in 710 ml on schooldays of milk ‘substitute’ that has the same macronutrient and very nearly the same micronutrient content as cow’s milk. (n=150) The substitute is a vegetable-based macronutrient substitute for milk. It consists of: almond milk (Pacific); coconut milk (Taste of Thai); and wheat gluten (King Arthur). A non-nutritive thickener (Simply Thick) made from xantham gum is added to give the consistency of whole milk. The Pacific almond milk is fortified with calcium and vitamin D. The recipe is found in Appendix 11.
5. 300 IU vitamin D supplements on schooldays (n=100). (the first month will follow the following schedule to parallel the milk “phase-in: 100 IU/day for three days; 200 IU/day for two days; 300 IU/day thereafter)
6. Larger dose vitamin D supplements once a month (n=100). The maximum daily dose of the “monthly supplement” will be 2000 IU, per Institute of Medicine upper limits for children.[Standing Committee on the Scientific Evaluation of Dietary Reference Intakes FaNB, Institute of Medicine: Dietary Reference Intakes for Calcium, Phosphorus, Magnesium, Vitamin D, and Fluoride. National Academy Press, Washington, D.C., 1997. <http://books.nap.edu/openbook.php?record_id=5776&page=285> ] The “monthly dose” will in fact be spread over several days at the start of each month. (See table 1, in Section L.3C.7 above, for the detailed schedule.)

With the exception of the unfortified milk arm (arm #3), all arms will get 14,200 IU of vitamin D over the three months. Parents of children in the unfortified milk arm will receive an equivalent amount of vitamin D supplements at the conclusion of the trial.

We will use vitamin D tablets produced by Nature Made.

Randomization method for intervention and control groups:

We will use a mix of block and individual-level randomization. Some children will receive supplements (1 of 2 supplement regimens), while other children will receive milks (one of 4 milks). Since the milk is more desirable to children than supplements, it would be unacceptable to randomize children in the same classroom to milk or supplement. However, we think it is acceptable to have one classroom in a school be a supplement classroom, and the other a milk classroom. We do this to minimize socioeconomic confounding; our primary concern here is having equivalent baseline nutritional status across intervention arms.

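### The seven-day 'monthly' course in Amendment 3 delivers at most 14,000 IU, less than the 14,200 to 15,400 IU that the revised schedule gives the daily arms, so the daily versus monthly 25(OH)D contrast is not at equal dose

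*Supplement*

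**What the plan says.** All of this is in the Fortification Study protocol and its amendments.

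- **Original schedule.** Table 1 and the Intervention Arms section give every arm except unfortified milk 14,200 IU over 50 school days. The daily supplement arm starts with a phase-in: "100 IU/day for three days; 200 IU/day for two days; 300 IU/day thereafter". The milk arms are phased in over the same first week.
- **Cap.** The Intervention Arms section says that the largest daily dose in the monthly arm "will be 2000 IU, per Institute of Medicine upper limits for children". Amendment 3 keeps to this, noting that its dosing "is within the tolerable upper limit of 2000 IU per day published by the Institute of Medicine".
- **Amendment 3, the latest dosing text.** The trial now runs "from January 26-March 20, including weekends", with 300 IU on each day in the milk and daily supplement arms. The amendment recalls that the monthly arm was meant to receive doses "for a total of 15000 IU over three months, the equivalent vitamin D dose as the milk and daily supplement groups". It says that the monthly dose must likewise fit into about 50 days, and continues: "We propose to do this by giving the children 1700-2000 IU per day for 7 days at the beginning of the trial". It gives no new total for this course.
- **Equal-dose premise.** The Sample size section says that all arms other than unfortified milk deliver an equivalent amount of vitamin D3. No amendment shown changes that sentence.
- **Use.** Daily versus monthly change in 25(OH)D is the first primary vitamin D comparison (Aim 1a). The later analysis plan repeats it as daily versus seasonal in the 25OHD models.

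**The concern.** The contrast is meant to show whether a few large doses work as well as small daily ones. It answers that only if both arms are scheduled to receive the same total. Seven days under a 2000 IU/day cap cannot reach the total that the amendment itself calls equivalent, nor the total implied by its dates.

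Hypothesis 1a is that daily dosing gives higher 25(OH)D than monthly dosing. A smaller total in the monthly arm pushes the result the same way, so part of any observed advantage for daily dosing could be a dose effect. The Sample size section also says that showing equivalence would be as useful as showing a difference, and a scheduled dose gap works against a clean equivalence statement.

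The models that adjust for completion do not repair this. Completion is the proportion of the assigned intervention received. A child who takes everything scores 100% in either arm, although the two schedules contain different amounts.

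**Working it through.** **Inputs.** The monthly course is 1700 to 2000 IU/day for 7 days. The daily arms get 300 IU/day from 26 January to 20 March 2009. Phase-in is 3 days at 100 IU and 2 days at 200 IU. The cap is 2000 IU/day. The pilot means are 43.1 and 66.1 nmol/L. Table 5 uses 100:100 and SDs of 12.5 and 25 nmol/L.

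**Reproducing the plan's totals.**
- 50 days with phase-in: 3×100 + 2×200 + 45×300 = 14,200 IU, as in Table 1.
- 50 days without phase-in: 50×300 = 15,000 IU, the figure in Amendment 3.

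**Daily arms on the amended dates.** Inclusive days: 6 + 28 + 20 = 54. With phase-in: 3×100 + 2×200 + 49×300 = 15,400 IU.

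**Monthly arm.** 7×1700 = 11,900 IU; 7×2000 = 14,000 IU.

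**Comparison.** Shortfall = (daily total − monthly total) / daily total. Bias = shortfall × (66.1 − 43.1) = shortfall × 23 nmol/L, assuming that response is proportional to dose and as large as the pilot rise.

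| Daily-arm total | IU/day needed over 7 days | Shortfall at 14,000 IU | Bias, nmol/L | Shortfall at 11,900 IU |
|---|---|---|---|---|
| 14,200 (50 days, phase-in) | 2029 | 200 IU, 1.4% | 0.3 | 16.2% |
| 15,000 (50 days, no phase-in) | 2143 | 1000 IU, 6.7% | 1.5 | 20.7% |
| 15,400 (54 days, phase-in) | 2200 | 1400 IU, 9.1% | 2.1 | 22.7% |

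Every figure in the second column is above the cap, so no seven-day course within it matches any of the three totals. The last column is an outer bound, since it needs 1700 IU on all seven days. The same formula would then give 0.162×23 = 3.7 to 0.227×23 = 5.2 nmol/L.

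**Effect on the test, with no true regimen difference.** SE = SD×√(2/100) = 1.77 (SD 12.5) or 3.54 (SD 25) nmol/L; k = bias/SE; two-sided 5% rejection = P(Z > 1.96 − k) + P(Z < −1.96 − k). Clustering is ignored.
- 14,200 IU, SD 12.5: k = 0.32/1.77 = 0.18, rejection about 5.4%.
- 15,000 IU: k = 1.53/1.77 = 0.87 or 1.53/3.54 = 0.43, rejection 14.0% or 7.2%.

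**The case against.** **The 15,000 IU is a recap.** It describes the superseded plan, and loosely, because that plan specified 14,200 IU. The amendment never says that the seven-day course totals 15,000 IU, and a reader should not infer that it does. This stands, and it is why 14,200 IU belongs in the comparison. Against that total the best-case gap is only 1.4%.

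**54 is a calendar count.** The amendment speaks of roughly 50 days and says "The intervention will still run the same total number of days". Closing blood draws might also fall inside the dates. That is fair, so 15,400 IU is one reading among three. But 50 days does not remove the shortfall.

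**A matching reading exists.** Amendment 3 describes the earlier plan thus: "We had originally planned to run the intervention from January 19 through the end of March, on schooldays only". With the one-week break it mentions, that is 10 + 20 + 22 − 5 = 47 days, or 700 + 42×300 = 13,300 IU with phase-in, exactly 7×1900. More generally, 14,000 IU covers up to 49 days with phase-in (700 + 44×300 = 13,900 IU). The 1700 to 2000 range may have been chosen this way. However, 47 to 49 days is fewer than the amended dates span, and the 47 comes from the schedule being replaced.

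**Timing already separates the arms.** Giving the whole course in the first week is an open and intended regimen difference, and a dose gap of a few per cent adds little to it. This supports a low grading. It does not make the equal-dose statement true.

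**A stronger inference to avoid.** A reader might compute 54×300 = 16,200 IU and claim a 13.6% best-case gap. That needs the phase-in to have been dropped, and no amendment clearly withdraws it.

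**Conclusion.** The point holds, as a minor one. On each reading of the revised schedule (14,200, 15,000 or 15,400 IU for the daily arms) the seven-day course falls short, by at least 1.4%, 6.7% or 9.1%. The equal-dose premise in the Sample size section therefore fails for the daily versus monthly (seasonal) 25(OH)D contrast, in the direction of hypothesis 1a.

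The likely bias is about 0.3 to 2 nmol/L. That rests on 2000 IU being given on all seven days, on a response proportional to dose, and on the pilot's 23 nmol/L rise. The pilot had no control group and ran from May to June, so its rise may include a seasonal part and overstate the dose effect. Lower daily doses within the stated range would widen the gap, but even the outer bound of 5.2 nmol/L is under half of the 12 nmol/L meaningful difference.

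A reader might infer that the primary comparison is invalid or the trial underpowered. The documents do not support that. Table 5 and the sample size do not depend on the dose total, and the growth analysis compares fortified with unfortified Mongolian milk, which the monthly arm does not enter.

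**What to change.** State the daily arms' total IU under the revised schedule, giving the number of dosing days and whether the phase-in applies. Then match it in the monthly arm with eight dosing days within the 2000 IU/day cap:

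- 8×1775 = 14,200 IU
- 8×1875 = 15,000 IU
- 8×1925 = 15,400 IU

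This costs one extra tablet day in one arm.

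If dosing is already done, remove the equal-dose statement from the Sample size section, describe the daily versus monthly/seasonal 25(OH)D contrast as regimen plus total dose, and report IU actually taken by arm. The milk monitors' compliance records already hold the data, so the cost is a change of wording and one descriptive table.

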Blood samples will be collected and cooled immediately before transportation to the Health Sciences University of Mongolia Laboratory, where they will be spun, aliquotted into 4 x 1ml cryotubes, and frozen. White cells (DNA) will be discarded. To guard against freezer failure, one set of aliquots will be kept in the electrical -70 freezer (with generator backup) at the HSUM laboratory, and the other set in a liquid nitrogen -80 freezer at the laboratory of [name], with whom we collaborated for the pilot study. Assays will be run in Canada, and will require shipment by express carrier on dry ice. We accomplished this during the pilot study, and are seeking even faster methods with the cooperation of Korean Air and courier services.

1. **Trained medical student volunteers will measure height, sitting height, weight, and grip strength at both baseline and at the conclusion of the study.** Trained medical volunteers will assess Tanner stage and rickets symptoms at baseline only.
2. Trained medical student volunteers will perform a dermatologic exam to derive Investigator Global AD Assessment (IGADA) and EASI score at both baseline and at the conclusion of the study.
3. Classroom teachers will complete the Classroom Behavior Questionnaire for each child at the beginning and end of the study. For a subset of students, trained medical student volunteers will perform the Continuous Performance Test with children at baseline and at the conclusion of the study. (The computer will generate dot matrix numbers (3..6..2..8..1..10..) that will appear on the CPT screen. The child will be asked to push a response button each time they see the target stimulus preceded by a certain number appear on the screen. The task should take approximately 15 minutes.)
4. **The first week of the milk intervention will be a ‘phase-in’ period, in which 236 ml/per day of milk or milk substitute will be consumed for the first three days, followed by 472 ml/per day over the next two days**. **In the second week, the full 710 ml protocol will be initiated**. The vitamin D supplement arms will be phased in accordingly (100 IU days 1-3, 200 IU day s 4-5; 300 IU thereafter for the daily supplement arm; 5200 IU will be given for the first monthly dose for those in the monthly supplement arm. See schedule in table 1.

Table 1. Schedule of vitamin D fortification/supplementation

|  | Schooldays | Daily IU in daily supplement and fortified milk arms | Monthly IU in monthly supplement arm |

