To determine sample sizes, we first debated the smallest clinically interesting contrast in vitamin D between arms. Since all arms (except the n=100 unfortified Mongolian milk arm) deliver the equivalent amount of vitamin D3, we anticipate small differences between them. We felt it would be as useful to definitively establish equivalency between arms as it would be to detect clinically meaningful differences; for that reason, we propose a well-powered study that can deliver tight confidence intervals. We felt that the minimum clinically meaningful difference would be 12 nmol/L (5 ng/ml). Accordingly, we designed a study to detect differences <12 nmol/L with 80% power.

In Table 5 below, we show the minimum standard deviation difference in mean 25(OH)D levels between the post-intervention arms, setting Type 1 error (alpha) to 0.05 and Type 2 error (beta) to 0.80. We used PASS statistical software for our calculations. These power calculations are conservative, in that they don’t take advantage of the pre-intervention data, which can be used to measure within-individual change. In our pilot study, we observed mean + standard deviation (s.d.) 25(OH)D levels of 43.1 + 12.0 nmol/L (17.3 + 4.8 ng/ml) at the outset of the intervention and 66.1 + 11.2 nmol/L (26.5 + 4.5 ng/ml) at the end of the one month intervention in Ulaanbaatar from May to June. These are consistent with data from adolescents in Boston winter (20.2 + 9.9 ng/ml) (Arch Pediatr Adolesc Med. 2004;158:531-537) and children in northern Spain in March (12.6 + 5.5 ng/ml).(**J Bone and Mineral Research 1998;13:544-548)** To translate the minimum detectable s.d. into clinically meaningful units of 25(OH)D, we assumed s.d.’s of 12.5 and 25 nmol/L (5 and 10 ng/ml).

Table 5.

| Contrast | N | Minimum Detectable SD units | Translation of SD into 25(OH)D units: smallest difference we could distinguish from zero with 80% power* |
| --- | --- | --- | --- |
| Monthly v. daily supplement | 100:100 | 0.40 | 5.0 to 10 nmol/L  (2.0 to 4.0 ng/ml) |
| Either supplement vs. Mongolian fortified milk; Mongolian unfortified vs. fortified milk | 100:150 | 0.36 | 4.5 to 9 nmol/L  (1.8 to 3.6 ng/ml) |
| Any supplement vs. Mongolian fortified milk | 200:150 | 0.30 | 3.7 to 7.5 nmol/L  (1.5 to 3.0 n/ml) |
| Contrast between any two fortified milks | 150:150 | 0.32 | 4.0 to 8.0 nmol/L  (1.6 to 3.2 ng/ml) |

*Assumes s.d. of 5-10 ng/mL for 25(OHD) comparisons

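### The 7-day course in Amendment #3 of the Fortification Study gives the former monthly arm at most 14,000 IU, less than the equal dose the plan states, so daily versus seasonal partly mixes dose with schedule.

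*Supplement*

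**What the plan says.** All references are to the Fortification Study.

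- **Equal dose as designed.** Under Intervention Arms, with the unfortified milk arm excepted, "all arms will get 14,200 IU of vitamin D over the three months". The Sample size section builds on this: because those arms "deliver the equivalent amount of vitamin D3, we anticipate small differences between them", it values establishing equivalence as much as detecting a difference.
- **Equal dose as recalled in Amendment #3.** The monthly arm was intended to receive its doses "for a total of 15000 IU over three months, the equivalent vitamin D dose as the milk and daily supplement groups". The amendment then says that, since daily dosing is being compressed into about 50 days, the monthly dose must be delivered in about 50 days too.
- **New course for that arm.** The amendment proposes "giving the children 1700-2000 IU per day for 7 days at the beginning of the trial". It mentions no later dose. The analysis plan calls this arm seasonal.
- **New daily schedule.** 300 IU every day, "from January 26-March 20, including weekends". The amendment adds that the number of intervention days is unchanged. It does not withdraw the phase-in described under Intervention (100 IU on days 1-3, 200 IU on days 4-5, "300 IU thereafter for the daily supplement arm").
- **Ceiling.** The maximum daily dose in the monthly arm "will be 2000 IU, per Institute of Medicine upper limits for children". Amendment #3 repeats this limit.
- **Use in the analysis.** Daily versus monthly change in 25(OH)D is the first primary vitamin D comparison (Aim 1a). The analysis plan keeps seasonal versus daily in items 4 and 5 of its Fortification models.

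No section gives a new total for either arm after Amendment #3.

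**The concern.** The comparison isolates schedule only if both arms are assigned the same amount of vitamin D. Amendment #3 restates that aim and then prescribes a course that cannot meet it. On the plan's stated totals the seasonal arm is planned to receive less, and Aim 1a predicts that daily dosing will give the higher 25(OH)D. A daily advantage could then come partly from dose, and the smaller dose would count against the seasonal arm if the aim were to show equivalence.

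The models do not remove the gap. Their only exposure covariate is completion, defined in the analysis plan as the proportion of the assigned intervention received. A fully compliant child scores 1.0 in either arm, whatever number of IU was assigned.

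**Working it through.** **1. Reproduce the plan's total (Table 1).**

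- Daily: (3 x 100 + 2 x 200 + 15 x 300) + 10 x 300 + 20 x 300 = 5,200 + 3,000 + 6,000 = 14,200 IU.
- Monthly: (2 x 2,000 + 1,200) + (2,000 + 1,000) + 3 x 2,000 = 14,200 IU.

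The arms were matched exactly, over 20 + 10 + 20 = 50 days. Amendment #3's 15,000 IU is 50 x 300, which leaves out the phase-in deduction of 3 x 200 + 2 x 100 = 800 IU.

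**2. Seasonal course after Amendment #3.** 7 x 1,700 = 11,900 IU; 7 x 2,000 = 14,000 IU.

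**3. Daily course after Amendment #3.** 26 January to 20 March 2009 inclusive is 6 + 28 + 20 = 54 days. If the unchanged number of days means Table 1's count, it is 50.

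| Daily arm | Total (IU) | Gap at 2,000 IU x 7 | Gap at 1,700 IU x 7 |
|---|---|---|---|
| 50 days, phase-in | 15,000 - 800 = 14,200 | 200 (1.4%) | 2,300 (16.2%) |
| 50 days, flat | 15,000 | 1,000 (6.7%) | 3,100 (20.7%) |
| 54 days, phase-in | 16,200 - 800 = 15,400 | 1,400 (9.1%) | 3,500 (22.7%) |
| 54 days, flat | 16,200 | 2,200 (13.6%) | 4,300 (26.5%) |

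Percentages are of the daily total.

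**4. Could 7 days be enough?** 14,200 / 7 = 2,029 IU per day and 15,000 / 7 = 2,143 IU per day. Both exceed the 2,000 IU ceiling.

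**5. Scale in 25(OH)D (assumed).** The documents give no dose-response slope. A rough one comes from the pilot: a rise from 43.1 to 66.1 nmol/L in one month on 710 ml of fortified milk a day. Taking that as 300 IU for 30 days, 23.0 / 9.0 = 2.56 nmol/L per 1,000 IU. The pilot had no control group and ran from May to June, so I treat this as an upper value and also show a quarter of it. The response is taken as linear.

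| Gap (IU) | Full slope (nmol/L) | Quarter slope (nmol/L) |
|---|---|---|
| 200 | 0.5 | 0.1 |
| 1,000 | 2.6 | 0.6 |
| 1,400 | 3.6 | 0.9 |
| 2,200 | 5.6 | 1.4 |
| 4,300 | 11.0 | 2.7 |

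The plan's minimum meaningful difference is 12 nmol/L. Table 5 gives 5.0 to 10 nmol/L as detectable with 100:100.

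**6. Effect on the test.** Two-sided t test, 100 per arm, alpha 0.05, no true schedule effect. The noncentrality is (difference / SD) x sqrt(50). A 1,000 IU gap at full slope is 1.02 ng/ml. With SD 5 ng/ml the noncentrality is 0.204 x 7.07 = 1.45, and the chance of p < 0.05 is 30%; with SD 10 it is 11%. At quarter slope the chances are 6.5% and 5.4%. For 200 IU at full slope they are 6% and 5.2%.

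**The case against.** The strongest reply is that the gap may be trivial. Amendment #3 says the number of days is unchanged, Table 1 has 50, and the phase-in was not withdrawn. The daily total is then 14,200 IU, and seven doses of 2,000 IU fall only 200 IU short. This reading is reasonable, and on it the gap can be ignored if every dose is 2,000 IU.

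A reader might infer that the seasonal total lies below every possible daily total. The documents do not support that. Reading about 50 days as 49, with the phase-in, gives 700 + 44 x 300 = 13,900 IU. If the phase-in fills a seven-day first week, 3 x 100 + 4 x 200 + 43 x 300 = 14,000 IU, which is exact equality. Both readings, however, fall short of the 15,000 IU that the amendment names as its target, and equality still needs close to 2,000 IU on each of the seven days.

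A reader might also take 11,900 IU as a likely total. That requires all seven doses at 1,700 IU. The amendment describes the former schedule as a range too, and Table 1 shows doses there varying by day to reach a fixed sum. The range may therefore mean mixed daily doses, and the largest gaps should be read as outer limits.

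Delivered dose may also differ from planned dose. The daily arm has about 50 doses to miss and the seasonal arm seven, so incomplete intake could narrow the gap. Finally, the growth paper's main contrasts (vitamin D versus placebo, fortified versus regular Mongolian milk) are untouched. These points limit the size and reach of the problem. They do not let the prescribed course reach the stated dose.

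**Conclusion.** The point holds in a limited form. The 7-day course cannot deliver the equal dose the plan states, whether that is 15,000 or 14,200 IU, without exceeding 2,000 IU per day. The mismatch lies within the current dosing text of Amendment #3, which names the equivalent dose, requires its delivery and then prescribes less.

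At 2,000 IU per day the planned shortfall is 1,000 IU (6.7%) against the amendment's own figure, 200 IU (1.4%, negligible) against 14,200 IU, and 1,400 to 2,200 IU if daily dosing fills all 54 days. It is larger if doses are nearer 1,700 IU. On the stated totals it favours the daily arm, so primary comparison 1 and the seasonal-daily contrast in items 4 and 5 of the models partly mix dose with schedule.

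The size of the bias is uncertain. Even the outer gap at the full pilot slope stays below 12 nmol/L, so a clinically meaningful spurious difference is unlikely. A reader might infer that a false significant result is probable, but that would need a large gap, the full uncontrolled slope and the smaller SD together. The matter is worth correcting because the correction is cheap, and because equivalence of these arms is one of the stated purposes.

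**What to change.** State one planned total for the daily and seasonal arms, say whether the phase-in applies and how many days are dosed, and set the seasonal course to match within 2,000 IU per day:

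- 8 x 1,875 = 15,000 IU;
- 8 x 1,775 = 14,200 IU, if that is the daily total;
- 8 x 1,925 = 15,400 IU, for 54 days with the phase-in.

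Fix the dose for each day in place of a range. The cost is one more dosing day in one arm, with the last dose one day nearer the final blood draw. Sample size, visits and models stay as they are.

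If dosing is already complete, report planned and delivered IU per arm beside the seasonal-daily estimate, and describe that contrast as schedule plus dose unless the totals match. This costs a table row and a sentence.
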